### Study objective and hypotheses

This study aims to evaluate the effectiveness of a Web-based tailored intervention, *TAVIE en santé*, in supporting PLHIV to adopt health promoting behaviours, such as smoking cessation, being physically active and eating healthy.

The primary hypothesis is that at the 6-month follow-up, a significantly higher proportion of experimental group (EG) participants will have succeeded in changing the specific health behaviour that they individually selected (smoking cessation being physically active or healthy eating) when compared with the control group (CG) participants. The secondary hypothesis is that at the 3-month follow-up, compared with CG participants, EG participants will show significantly higher scores on intention, attitude, and perceived control regarding the adoption of their chosen health behaviour.

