### Analysis

Descriptive statistics will be used to compare the participants in the two groups with means, medians, standard deviations, and inter-quartile ranges for continuous and frequency distributions for categorical and binary variables. Any variable for which the difference between the two arms is considered clinically important will be adjusted through multivariable analyses. The principal analyses will focus on testing the hypothesized differences between the two trial groups using the Intention-to-Treat (ITT) analysis.

The primary outcome of the success/failure in the adoption of the chosen health behaviour at 6 months will be analyzed as a binary outcome. Accordingly, the primary hypothesis will be tested with the 2-tailed chi-square test, with 1 degree-of-freedom (df), at α = 0.05 significance level. Next, to adjust the intervention effect for potential confounders, we will build a multivariable logistic regression with adjustment for any baseline characteristics for which the descriptive analyses indicate a clinically important difference between the two groups. The multivariable model will also adjust for baseline values of the chosen health behaviour. In the multivariable logistic regression, the effect of the intervention will be estimated by the adjusted Odds Ratio, with 95 % CI, and its statistical significance will be tested by the model-based 1-df Wald chi-square test at 2-tailed α = 0.05. During ITT analyses, all participants will be assessed in their respective randomization group as to whether they are following the procedure or have been lost to attrition during the follow-up. In this manner, all participants lost to follow-up before 6 months will be assigned a ‘failure’, regardless of the group to which they were assigned randomly. This approach is conservative because it reduces the estimated difference between the two randomization groups.

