The secondary outcomes of intention, perceived behavioural control, and attitude, will be evaluated at the 3-months follow-up, and analysed as continuous variables. Thus, the same analytical methods will be used for all these outcomes. The distribution of the outcome scores will be assessed for normality of residuals using the Shapiro-Wilk test. We will assign the individual baseline score for a given outcome to participants who fail to provide data for a given outcome. To test the statistical significance of the un-adjusted difference between the mean values of a given (possibly transformed) outcome observed in the two trial arms at 3 months, we will use the 2-tailed independent-groups student’s *t*-test at α = 0.01. Multivariable linear regression will be used to adjust the estimation and testing of the intervention effect for potential confounders, for which the descriptive analyses indicate a clinically important difference between the two groups. In multivariable linear regression, the effect of the intervention will be estimated by the adjusted mean difference, with 95 % CI, and its statistical significance will be tested by the model-based F-test with 1-df in the numerator, at 2-tailed (Bonferoni-corrected) α = 0.01.

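### The Bonferroni-corrected alpha of 0.01 does not follow from the three secondary outcomes named, and the 95% CI beside it is at a different level (minor)

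*Protocol article*

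**What the plan says.** The secondary hypothesis (protocol article, Study objective and hypotheses) is that at 3 months "EG participants will show significantly higher scores on intention, attitude, and perceived control regarding the adoption of their chosen health behaviour". The Analysis section has the same three outcomes at the same single time point: "The secondary outcomes of intention, perceived behavioural control, and attitude, will be evaluated at the 3-months follow-up, and analysed as continuous variables".

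Each outcome is then tested twice at the same level:

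- Unadjusted: "we will use the 2-tailed independent-groups student’s *t*-test at α = 0.01".
- Adjusted, in a linear regression: "model-based F-test with 1-df in the numerator, at 2-tailed (Bonferoni-corrected) α = 0.01". Only here is the level called Bonferroni-corrected.

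For the regression, "the effect of the intervention will be estimated by the adjusted mean difference, with 95 % CI".

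Neither a family-wise level nor a number of comparisons is given for the correction. The only other significance level in the article is that of the primary outcome: "the primary hypothesis will be tested with the 2-tailed chi-square test, with 1 degree-of-freedom (df), at α = 0.05 significance level".

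**The concern.** The article names both a method and the threshold it is meant to produce. For the three outcomes listed, and at the only overall level used elsewhere, the method gives a different threshold. A reader cannot recover from 0.01 which tests form the family or what family-wise level is intended.

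The interval is also at a different level from the test. For the primary outcome a 95% CI accompanies a test at 0.05, so the two agree. For the secondary outcomes the 95% CI is kept while the test moves to 0.01.

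At stake is power on the trial's formal secondary hypothesis, which concerns the determinants the intervention is designed to change. The published results may also be hard to read, because the interval and the test will seem to disagree over a range of p-values.

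**Working it through.** **Inputs**

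- Three secondary outcomes at one time point (Study objective and hypotheses; Analysis).
- Stated level per outcome: 0.01, two-sided (Analysis).
- Family-wise level: taken as 0.05. This is an assumption, borrowed from the primary test.
- 375 participants per arm (Population, study setting and sample size). All of them enter the secondary analysis, because the Analysis section gives participants without follow-up data their baseline score.
- Standardized differences of 0.20 and 0.25: assumed for illustration, since the article gives none for the cognition scores.

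**Step 1: trying to reproduce 0.01.** Bonferroni level = 0.05/k.

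| Family | k | Level |
|---|---|---|
| Three secondary outcomes | 3 | 0.0167 |
| Primary plus three secondary | 4 | 0.0125 |
| Five tests (not described in the article) | 5 | 0.0100 |
| Three outcomes, each tested unadjusted and adjusted | 6 | 0.0083 |

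Šidák for three outcomes gives 1 − 0.95^(1/3) = 0.0170. Only k = 5 gives 0.01 exactly. The four-test value becomes 0.01 if it is rounded to two decimals.

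**Step 2: error control.** With one deciding test per outcome, the Bonferroni bound at 0.01 is 3 × 0.01 = 0.03. If the tests were independent, the family-wise error would be 1 − 0.99³ = 0.0297, against 1 − (1 − 0.0167)³ = 0.049 at 0.0167. Both lie below 0.05.

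**Step 3: power.** The critical values are 2.394 at 0.0167 and 2.576 at 0.01. For a standardized difference d and n per arm, power ≈ Φ(d√(n/2) − z).

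- d = 0.20, n = 375: d√(n/2) = 0.20 × 13.69 = 2.739. Power is Φ(2.739 − 2.394) = 0.635 at 0.0167 and Φ(2.739 − 2.576) = 0.565 at 0.01.
- d = 0.25, n = 375: d√(n/2) = 3.423. Power is 0.848 at 0.0167 and 0.802 at 0.01.

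A comparison that does not depend on d: an outcome with 80% power at 0.0167 has Φ(2.394 + 0.842 − 2.576) = 0.745 at 0.01. To recover 80% needs ((2.576 + 0.842)/(2.394 + 0.842))² = 1.116 times the sample, about 12% more. The 80% is only a reference point; the article claims no power for these outcomes.

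**Step 4: interval against test.** A two-sided test at level α corresponds to a 100(1 − α)% CI. That is 99% for 0.01, 98.33% for 0.0167 and 95% for 0.05. The 99% interval is 2.576/1.960 = 1.31 times as wide as the 95% interval. So any result with 0.01 < p < 0.05 has a 95% CI that excludes zero and a test that is not significant.

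**The case against.** The strongest reply has four parts.

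- **A stricter level is still valid.** Any per-test level at or below the family-wise level divided by the number of tests protects the family. This stands. A reader might infer from a mis-stated correction that the secondary claims are exposed to excess false positives. The document does not support that: the level errs on the safe side.
- **The intended family is not stated.** The 0.0167 rests on a borrowed 0.05. Counting the primary outcome gives 0.0125, which is 0.01 at the two decimals the article uses for alpha, and a fuller protocol or SAP may define the family. This stands in part. It rules out calling 0.01 a proven arithmetic slip. It does not explain the figure, because the article describes neither a four-test family, nor rounding, nor a family-wise level of 0.03. The article itself chose to state the threshold and the method together.
- **The CI has no decision role.** The Analysis section uses the interval for estimation and gives significance to the F-test. A reader might infer that the plan allows two opposite verdicts. It does not: for p between 0.01 and 0.05 the regression's formal answer is non-significant. What remains is a reporting mismatch that the text does not flag.
- **The trial was sized on the binary primary outcome.** No power is promised for the cognition scores, and with an assumed difference of 0.25 power is still 0.802 at 0.01. This also stands. The loss is real but modest, and it depends on the assumed effect.

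**Conclusion.** The point holds as a minor correction. For the three outcomes named, and assuming a family-wise 0.05, the Bonferroni level is 0.0167. The stated 0.01 matches no family the article describes.

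The consequence is avoidable loss of power: about 7 percentage points at an assumed standardized difference of 0.20 (0.635 to 0.565), and about 5 at 0.25 (0.848 to 0.802). Type I error is not inflated, provided one test per outcome decides. The article gives the same 0.01 to both the t-test and the F-test and does not say which of them settles the hypothesis.

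The 95% CI is not at the level of the test, so results with 0.01 < p < 0.05 will look inconsistent in print although the regression's decision rule is clear. The primary hypothesis, its test and its level are unaffected.

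**What to change.** Before outcome data are seen by arm, amend the secondary paragraph of the Analysis section as follows.

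1. State the family (three cognition outcomes at 3 months) and its family-wise level.
2. Either set the per-outcome level to 0.05/3 = 0.0167, or use Holm over the three outcomes, which keeps the same family-wise level and is never less powerful. Alternatively, keep 0.01, declare it a deliberately stricter level, and drop the Bonferroni label.
3. Name one deciding test per outcome, the t-test or the regression F-test. The other is supportive.
4. Report CIs at the matching level (98.33% for 0.0167, 99% for 0.01), or keep 95% and label the intervals as unadjusted and not used for the decision. Fixed 98.33% intervals do not reproduce Holm decisions, so with Holm the label is the simpler choice.

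If the deciding test is to adjust for the baseline score of the outcome, that must be added. The secondary regression now adjusts only for characteristics with a clinically important imbalance; baseline adjustment is specified only for the primary logistic model.

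The cost is a short amendment, with no change to data collection or sample size. Moving from 0.01 to 0.0167 relaxes a prespecified threshold, so it should be dated and justified. Keeping 0.01 needs only wording, at the price of the power shown above.

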### Ethics

#### Research ethics approval

In Quebec, this research protocol has been approved by the Research Ethics Board (REB) of the Centre Hospitalier de l’Université de Montréal (CHUM) following a multicentre research project protocol. The CHUM REB’s approval will then be forwarded to the other local study sites in Ontario and British Columbia, which will then seek the approval of their respective boards.

#### Consent

Due to the online nature of this study, the informed consent will be obtained online. To pique the interest of potential participants and render the study’s Website more dynamic and interactive, video clips will be posted, containing information about the study. In one of them, a peer will present specific information about the study (goal, modalities of participation, eligibility criteria, confidentiality, financing, etc.). Consent to participate will be presented in the form of a statement to be read and approved by clicking on a button “I agree to participante” [43]. A “Withdraw” page will always be available so that participants have the freedom to withdraw from the study at any time.

#### Confidentiality

The data collected online will be stored on a secure server located at the Research Centre of the CHUM and accessible to the research coordinator and principal investigator only. To protect the participants’ identity, an e-mail address and a login name known only to the research coordinator and the system administrator will be requested of participants. This information is necessary to ensure follow-up while respecting confidentiality, as pointed out by Michalak and Szabo [46]. Firewalls, data encryption, password protection, and separation of socio-demographic data from experimental data will reduce the risk of unauthorized access to confidential content by a third party [47, 48].

## Results

### Study Website description

A Website was created to promote and conduct this online study (see Appendix 3). As suggested by Hershberger and Coll. (2011), this Website was designed to communicate information, establish credibility, and facilitate contact [49]. Videos, animation, text, and PDF files are used to describe the purpose and implications of the study to the participants. All materials were prepared with ease of comprehension in mind. To inform participants about the partners of the study, we created a page to display the logos of the University’s affiliations of the investigators, financing organizations and recruiting sites. To facilitate communication, a “Contact Us” navigation tab, containing information on technical support or the reaching the research coordinator, is visible in every page of the Website.

### Study flow diagram

Once participants enrol in the study, they will follow different “pathways” over the 6 months of the study. The pathways depend on the chosen language and behaviour. During the enrolment process, participants will choose the language they prefer (French or English). The behaviour they choose in the baseline questionnaire (smoking cessation (SC), being physically active (PA), following a healthy eating (HE)) will impact randomization and follow-up questionnaires (t_1_ and t_2_). Therefore, there will be six pathways, as illustrated in Fig. 2.

**Fig. 2 Fig2:**
[figure not shown]
Study flow diagram

## Discussion

### Challenges and sources of bias

The study will be conducted entirely online, which poses various challenges in terms of participants’ selection and data collection [50]. One of our earlier online studies established the feasibility of the proposed research methodology and will serve as a guide to participants’ selection and data collection [43]. For instance, to prevent participants from registering more than once, the computer system will screen them to verify whether they meet the eligibility criteria. The design of the online questionnaire will only allow answering one question at a time and will not allow backtracking.

The study design will be controlled as best as possible but participants will not be totally blinded to group assignment. The CG will receive a detailed list of Websites providing relevant information related to health behaviour and available resources and services. Group equivalence will be ensured through random assignment and–if necessary–statistical adjustments, through multivariable regression modeling, for any potential imbalance in the distribution of any relevant baseline characteristic will be performed. Measures will be taken to ensure intervention fidelity/consistency by documenting all aspects of the intervention. Moreover, the intervention’s parameters will be recorded (number of pages visited), thus making it possible to obtain a reliable picture of the actual intervention intensity: duration and frequency of the intervention.

To reduce contamination bias, participants will be sensitized to the importance, from a research viewpoint, of not sharing with others the intervention material to which they will have access during the study. In any event, given that one of the particularities of the intervention is that it is “tailored”, the personalized feedback and information received is unlikely to be relevant to another participant. A selection bias will be inevitable because participants invited to participate in the study must necessarily have Internet access [51]. Given that the size and demographic characteristics of the online population are different from those of the off-line population [52–54], the results of the study will not be generalizable to PLHIV as a whole [55]. Given that many PLHIV are living on fixed incomes and for whom personal internet access may not be available, this constitutes a limitation of the planned intervention; however, for those who are able and willing to use technology, *TAVIE en santé* provides a potential health promoting and reinforcing resource.

### Projected impacts, benefits, and transfer of the study

Until now, most of the studies testing the efficacy of Web-based tailored health behaviour change interventions have been designed and conducted among the general population, were more preventive in nature and did not involve support for complex tasks required in self-management of chronic conditions (Lustria et al., 2013). According to Murray (2012), Web-based interventions for people with long-term conditions remain a challenge and may be less successful. The aim of the study is to evaluate an innovative Web-based tailored intervention for encouraging PLHIV to adopt specific health behaviours. This study will yield new results about the efficacy of Web-based tailored health behaviours change interventions in the context of chronic diseases (chronically ill patients).

Given the current short supply of specialists in healthcare and in the area of HIV-related services, *TAVIE en santé* offers clinicians an complementary instrument to support their professional practice and meet their clientele’s needs with a minimum investment. As it consists essentially of simulated interactions between a virtual nurse and the PLHIV, all that is needed is to provide minimal remote computer support services available in case of technical problems. This computer innovation affords the system administrator the flexibility to add and modify page without always having to resort to a Web developer. Thus, it reduces the costs of the system and facilitates the implementation of solutions over the long term in a normal context of clinical practice.

## Appendix 1

*TAVIE en santé* screenshot.

## Appendix 2

Examples of *TAVIE en santé* PDF tool for participants.

## Appendix 3

Study website screenshot.

## Abbreviations

ART: Antiretroviral therapy
CI: Confidence interval
CHUM: Centre Hospitalier de l’Université de Montréal
HE: Healthy eating
ICT: Information and communications technologies
ITT: Intention-to-Treat
PA: Physical activity
PLHIV: Persons living with HIV
REB: Research Ethics Board
SC: Smoking cessation
TPB: Theory of planned behavior
